### *Statistical Analysis of Secondary Endpoints*

***Intestinal inflammation and fecal microflora analysis:*** a descriptive analysis will be performed. Continuous variables will be expressed as mean ± standard deviation (SD), while categorical variables as proportions. The significance of the differences between the groups will be assessed by the chi square test and Fisher’s exact test for dichotomous variables. Continuous variables will be compared with the Student t test and the Mann-Whitney test. A two-sided test was used to indicate statistical significance at a p value of <0.05.

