Our hypotheses are supported by preliminary data from our centre. In a subsequent study, the incidence of intestinal inflammation was investigated in a population of 30 CF children, otherwise unselected [6]. Fecal calprotectin and rectal nitric oxide concentration in rectal dialysis bags were used as non invasive markers of intestinal inflammation [6]. It was observed that intestinal inflammation was very frequent in CF. Mean calprotectin values were 4 times above normal in CF children. Nitric oxide rectal production was also increased, which supports the concept that the distal intestine represents a target organ in CF disease. In a trial with the probiotic strain *Lactobacillus rhamnosus* GG (LGG) in children with CF colonized with *Pseudomonas aeruginosa,* calprotectin and nitric oxide concentrations were decreased and values of these inflammatory marker did not return to fully normal values [6].

In a subsequent prospective, randomized, placebo-controlled, cross-over study, we investigated the incidence of pulmonary exacerbations and hospital admissions in CF children colonized with *Pseudomonas aeruginosa* [7]. Pulmonary exacerbations and of hospital admissions were fewer in patients receiving the probiotic LGG than in patients treated with oral rehydration solution (ORS). Probiotics administration also resulted in a slight increase in forced expiratory volume in 1 sec (FEV1). These data suggest that probiotics may delay respiratory impairment in CF children and support a relationship between intestinal and pulmonary inflammation.

Although the evidence available is largely preliminary and should be regarded with caution, our data implicate colonic intestinal microflora in the pathogenesis of CF, as follows:

- Colonic intestinal microflora is changed in CF as a result of changes in intestinal environmental and aggressive therapy.
- Mild to moderate intestinal inflammation is frequent in CF, at least in part, as a consequence of abnormal microflora composition.
- Administration of selected probiotics reduces intestinal inflammation and also exerts beneficial effect on intestinal microbiota .

The intestine, and specifically the intestinal microflora, may therefore be an important target for treatment in CF. The administration of probiotics is a promising treatment approach for children who are on heavy load of antibiotics.

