***Study design***

Study activities are reported in the timeline (Table 1).

| **Parameters** | **Visit 1a** | **Visit 2b** |
| --- | --- | --- |
| Written informed consent | x |  |
| Randomization |  | x |
| Clinical examination | x | x |
| Genetic analysis (if not already performed) | x |  |
| Demographic | x |  |
| Anthropometric | x | x |
| Intestinal inflammation | x | x |
| Microflora |  | x |
|  |  |  |

Study design

Patients meeting the inclusion criteria will be enrolled and randomly assigned to the treatment or placebo group arm. Patients randomized to the treatment arm will receive 6x109 CFU of LGG once a day for a 1-month period. Patients randomized to the placebo group will receive placebo once a day for 1 months. LGG and placebo formulations will be masked and coded appropriately to ensure blindness. LGG formulations will be composed of maltodextrin (163 mg), gelatine capsule (75 mg), LGG (60 mg), magnesium stearate (2 mg). The placebo composition will be maltodextrin (223 mg), gelatine capsule (75 mg) and magnesium stearate (2 mg). LGG and placebo capsules will be identical in appearance, taste and color and only a numeric code will differentiate the two formulations.

For these patients systemic inflammation and intestinal microflora using Fluorescent in situ Hybridization will be evaluated before starting treatment and at the end of it (0 and 1 month

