***Specific statistical analysis***

# *Statistical Analysis for primary endpoints*

**INTESTINAL INFLAMMATION:** The binary outcome variable is the presence of at least one intestinal inflammation episode for subject j in cluster i (i=1,..,N, j=1,…n). Based on the results of Bruzzese et al[6], a proportion of subjects with at least 1 episode of intestinal inflammation of 0.90 is expected; a reduction of 30% of such proportion is considered clinically relevant (0.90 vs 0.63). These values determine an odd of experiencing at least one intestinal inflammation episode 0.19 times smaller in the treatment group than in the control group. A intra-cluster correlation coefficient () between the two time occasions of 0.6 is assumed (this is rather a cautionary value because a smaller coefficient is expected) With a one-sided  of 0.025 and a statistical power (1-β) of 0.80, 35 subjects per treatment group are needed to detect such difference in favour of the LGG compared to placebo after twelve months. Alternatively, by using the sample size obtained for powering the analysis of pulmonary exacerbations, all other things being equals, a power of 92% will be reached.

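### Intestinal inflammation is powered as a yes/no outcome and tested without the scheduled baseline calprotectin; a baseline-adjusted analysis of log calprotectin should be the main comparison

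*Protocol*

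**What the plan says.** The Endpoints section lists modification of intestinal inflammation as a primary endpoint. The section Statistical Analysis for primary endpoints then makes it binary: "The binary outcome variable is the presence of at least one intestinal inflammation episode". It continues that "a proportion of subjects with at least 1 episode of intestinal inflammation of 0.90 is expected" and that "a reduction of 30% of such proportion is considered clinically relevant (0.90 vs 0.63"). It adds that a correlation "between the two time occasions of 0.6 is assumed", and ends with one-sided alpha "of 0.025 and a statistical power (1-β) of 0.80, 35 subjects per treatment group are needed". That section names no test.

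The only named tests are in Statistical Analysis of Secondary Endpoints, which covers intestinal inflammation and microflora again. Dichotomous variables get chi-square and Fisher tests. For the rest, "Continuous variables will be compared with the Student t test and the Mann-Whitney test". Summaries are means with SD. No baseline covariate, change score or log scale is mentioned.

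The data would support more. The Intestinal inflammation section measures calprotectin as a concentration by ELISA, with reference bands of 0 to 50, 50 to 100 and above 100 micrograms/g. Table 1 has the row "Intestinal inflammation | x | x", so it is scheduled at both visits.

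**The concern.** The endpoint is a change, each child has a pre-treatment value, and the stated tests compare two groups without using it. Chance imbalance in baseline calprotectin between small arms would go uncorrected.

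The yes/no outcome discards information as well. A cut-off registers only falls that cross it. The protocol's own background reports that, with LGG, "calprotectin and nitric oxide concentrations were decreased and values of these inflammatory marker did not return to fully normal values", so falls that stop short of normal are to be expected. Eligibility does not require a raised calprotectin, so a child below the cut-off at entry cannot improve on the binary scale.

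A t test on untransformed values has a different weakness. Calprotectin is positive and, according to the Significance section, averages four times normal in these children. It is therefore probably right-skewed, and a few high values would inflate the SD. Finally, listing two tests for each type of variable with no rule for choosing leaves two p values per variable.

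**Working it through.** **Inputs from the protocol.** Proportions 0.90 and 0.63; one-sided alpha 0.025 (z = 1.960); power 0.80 (z = 0.842); 35 per arm; two-sided 0.05 for the named tests.

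**Assumptions not in the protocol.** Log calprotectin is normal with SD 1. The baseline-to-end correlation r on the log scale is 0.3 to 0.6. The smaller-trial scenario of 11 per arm is half of the 22 stable CF children in the FISH section, with a 1:1 split assumed. The binary outcome is a single cut-off at the end of treatment; the protocol does not define an episode.

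**Step 1: the plan's own figure.** With unpooled variance, n = (0.90×0.10 + 0.63×0.37)×(1.960+0.842)²/0.27² = 0.3231×7.849/0.0729 = 34.8, so 35 per arm. The log-odds formula gives 43.6; multiplied by (1+0.6)/2 = 0.8 this is 34.9, also 35. The pooled-variance formula gives 38. The odds ratio is (0.63/0.37)/(0.90/0.10) = 0.19, as stated. The plan's figure reproduces.

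**Step 2: the same effect on a continuous scale.** The shift that moves 90% above a cut-off to 63% is z(0.90) − z(0.63) = 1.282 − 0.332 = 0.95 SD. With log-SD 1 this is a geometric-mean ratio of exp(−0.95) = 0.39.

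**Step 3: n per arm for 80% power** (normal approximation; a t-based calculation adds about one).
- Binary: 35 to 38.
- Log values, unadjusted: 2×7.849/0.95² = 17.4, so 18.
- ANCOVA, variance multiplied by 1 − r²: 17.4×0.91 = 15.8, so 16 (r = 0.3); 17.4×0.64 = 11.1, so 12 (r = 0.6).
- Unadjusted comparison of log changes, variance multiplied by 2(1 − r): 17.4×1.4 = 24.4, so 25 (r = 0.3); 17.4×0.8 = 13.9, so 14 (r = 0.6).

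Not dichotomising saves 17 to 20 children per arm. Adjustment then saves 2 (r = 0.3) to 6 (r = 0.6), which corresponds to removing r² = 9% to 36% of the variance.

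**Step 4: simulated power of the named tests and of ANCOVA.** Repeat simulations agree to about 2 percentage points. The log-SD affects only the untransformed t test.

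| Test | 35 per arm, 0.95 SD | 11 per arm, 0.95 SD | 35 per arm, 0.67 SD, r = 0.6 |
|---|---|---|---|
| Fisher | 70% | 15% | 33% |
| Chi-square | 79% | 29% | 44% |
| t, untransformed | 87% | 37–38% | 59% |
| Mann-Whitney | 97% | 54% | 76% |
| ANCOVA, log scale | 98–99.8% (r 0.3–0.6) | 59–74% (r 0.3–0.6) | 92% |

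**The case against.** **The protocol does not say the tests are on raw end values.** Correct. That reading rests on the mean-and-SD summary and on silence, and the word modification could mean change scores. But comparing changes is no substitute for adjustment. By Step 3 it needs 25 per arm at r = 0.3, worse than ignoring baseline (18), and 14 against 12 at r = 0.6.

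**Covariates and transformations are commonly left to the SAP, and this section calls itself descriptive and secondary.** As mere missing detail the point would fall. Here, however, the protocol itself fixes a binary outcome and names the tests, and they are the only tests given for a primary endpoint.

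**Mann-Whitney already does well.** This stands. It is unaffected by a log transformation and has about 97% power at the stated 35 per arm, so ANCOVA adds only 1 to 3 points there. A reader might infer that baseline adjustment recovers large power at no cost. The figures do not support that: most of the gain comes from leaving the yes/no scale.

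**The binary outcome is not blind to partial improvement.** This also stands. A child who falls from above 100 into the 50 to 100 band is still not normal but does cross the 100 cut-off. The outcome is insensitive to falls that do not cross, and no more than that.

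**The clinically relevant difference is stated as a proportion.** True. The documents give no relevant geometric-mean ratio, which is the reason to keep the proportion as a supportive result.

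**Conclusion.** The point holds as a recommended improvement in method, not as a fatal flaw. Against the powered binary analysis the gain at 35 per arm is about 20 to 30 points of power. Against a t test on untransformed values it is about 11 to 13 points, and against Mann-Whitney 1 to 3. Adjustment itself matters mainly when the sample or the effect is smaller than planned: at 11 per arm, 54% with Mann-Whitney against 59 to 74% with ANCOVA; for a 0.67 SD shift at 35 per arm and r = 0.6, 76% against 92%.

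These sizes rest on log-normality, log-SD 1 and an assumed r. The documents give no SD or correlation for log calprotectin. The 0.6 in the sample-size paragraph belongs to the binary outcome, and the protocol itself expects a smaller value. A reader might also infer that the trial has 11 children per arm and a severe loss of power. That is only a scenario taken from a past-tense account of FISH samples; the stated size is 35.

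**What to change.** - Make the main between-arm analysis of intestinal inflammation an ANCOVA of log calprotectin at 1 month on arm and log baseline calprotectin, reported as a geometric-mean ratio with 95% CI. State the assumed log-SD and correlation.
- Keep the proportion above 100 micrograms/g as a supportive analysis, because clinical relevance is stated as a proportion.
- Name one test per variable instead of two.
- Apply the same baseline adjustment to the FISH counts only once Table 1, which marks microflora at visit 2 alone, is reconciled with the Study design text, which has it at 0 and 1 month. Table 1 also places randomisation at visit 2. Visit 1 is pre-treatment on either reading, but the timing of visit 2 should be made explicit.

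The cost is wording and slightly more analysis, with no extra visit, sample or child. The downside is that the headline becomes a ratio rather than a proportion, and the documents offer no benchmark for how large a ratio matters.

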
To examine these hypotheses, a randomized, controlled, double blind multi-center study will be performed to determine the effect of daily supplementation of *Lactobacillus casei sps. Rhamnosus* (*Lactobacillus GG*) on GI and respiratory tract bacterial communities and to relate microbiological changes to primary and secondary clinical and immunological outcomes.

***Specific Aim 1. Define the CF gut microbiome by comparing stool samples from CF pediatric patients at baseline (prior to supplementation) to age matched healthy subjects.***

***Specific Aim 2.*** ***Determine the effect of daily Lactobacillus GG supplementation on GI bacterial communities of CF patients fed probiotic or placebo.***

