**Significance.**

It is becoming clear that intestinal microflora is a complex functional unit that lives with the host in a symbiotic relationship. The gastrointestinal tract harbors more than 1000 bacterial species, whose composition is a result of several factors including age, diet, antibiotics and other drugs. The hygiene hypothesis, also known as the theory of “old friends”, implicated intestinal bacteria in the regulation of the immune response [9]. Commensal bacteria drive the immune response by inducing a maturation pattern of dendritic cells that stimulate the regulatory T-cell response. Deficient exposure to the “old friends” or changes in intestinal microecology may lead to an abnormal immune response. There is evidence that a healthy intestinal microflora protects from allergy and other immune disorders [10] by driving the development of immune response toward protection against intestinal and extraintestinal infections, including respiratory infections [11-13].

Children with CF are at risk of an abnormal intestinal microflora, as a consequence of impaired CFTR function, a heavy antibiotic load, pancreatic enzyme supplementation and acid suppression treatment [14]. Our preliminary data (unpublished, see “Preliminary studies section”) indicate that CF patients have a peculiar microbiota. Lung disease, malnutrition and pulmonary inflammation occur very early in life in people affected by CF [15].

The intestine is a site of inflammation in CF. Using immunohistochemistry and intestinal morphometric analysis, Raia et al., identified duodenal mucosal T-cell activation in the absence of alterations of villous architecture in a subset of CF children at-risk of intestinal involvement because of recurrent vomiting or chronic diarrhea who underwent upper endoscopy [16]. The T-cell response was characterized by an increased infiltration of the lamina propria by mononuclear cells expressing ICAM-1, CD25 and IFN-gamma, and by an increased number of villous enterocytes expressing transferrin receptors.

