***Study population***

**Inclusion criteria will be:**

1. A confirmed diagnosis of CF documented by sweat chloride test over 60 mmol/L and confirmed by genotype analysis with the presence of F508del/F508del or F508del/other
2. Boys and girls between 2 and 18 years of age
3. Clinical stability at enrolment, defined as no clinical evidence of acute exacerbation, no modifications in the therapeutic regimen and no hospitalization in the last 2 weeks
4. Pancreatic insufficiency
5. Basal FEV1 above 50% of predicted value

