**Sample Collection and Handling for FISH evaluation**

FISH was performed on fecal samples collected from 22 CF children in stable clinical conditions, 20 age-matched healthy controls. Stools from 10 CF children on antibiotic treatment were also collected and analysed. CF children, in stable conditions, were then treated with LGG (6x109 cfu/die) or placebo for 4 weeks and intestinal microbiota was evaluated again immediately after their administration.. Based on the results obtained by DGGE and RT-PCR, we chose to investigate the presence of *Bacteroides* and *Eubacterium rectale* since both species were consistently reduced in CF children.

*F. prausnitzii* was chosen because it has been associated with the pathogenesis of inflammatory bowel diseases.

Fecal samples, fixed in Carnoy's solution and embedded in paraffin, were cut longitudinally into 4-μm sections, placed on SuperFrost slides (Thermo Scientific, Italy) and incubated with hybridization solution (20 mM Tris–HCl, 0.9 M NaCl, 0.1% SDS and 1% formamide, pH 7.4) with EUB mix positive control oligonucleotide probes (100 ng of EUB I, EUBII and EUBIII). For *Bacteroides*, *E.rectale* and *F. prausnitzii* the slides were incubated with hybridization buffer with 25 ng of their respective FISH probes for 45 min at 50 °C and evaluated by Nikon 80i Eclipse epifluorescence microscope. Using a Nikon DS-U2 color camera and NIS-Elements imaging software (Nikon, Tokyo, Japan). Bacteria were quantified by count within a 10×10–μm area of the microscopic field representative of the region of interest. The oligonucleotide probes used in this study were synthesized by MWG Eurofins (MWG Operon Ebersberg, Germany). All samples were analyzed with the Eub338 mix probe conjugated with fluorescein isothiocyanate (FITC, green signal) at the 5′-end (positive control, which is specific for all bacteria), and an appropriate species-specific probe was conjugated with a single fluorescent carbocyanine (Cy3, red signal) molecule.

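### The microflora tests ignore age, although the protocol names age as a determinant of the flora and matches the healthy controls on it: conservative in Aim 1, some precision lost in Aim 2

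*Protocol*

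**What the plan says.** The protocol's Significance section describes the intestinal flora as a community "whose composition is a result of several factors including age, diet, antibiotics and other drugs". The inclusion criteria admit "Boys and girls between 2 and 18 years of age". Specific Aim 1 compares the stool of CF patients, before supplementation, with that of "age matched healthy subjects", and the FISH section reports "20 age-matched healthy controls" beside 22 clinically stable CF children. For Aim 2, the Study design section says "Patients meeting the inclusion criteria will be enrolled and randomly assigned to the treatment or placebo group arm" and describes no stratification by age. Demographic data are collected at Visit 1 (Table 1).

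Modification of the microflora is one of the two primary endpoints. Its only stated analysis stands under Statistical Analysis of Secondary Endpoints. There, "The significance of the differences between the groups will be assessed by the chi square test and Fisher’s exact test for dichotomous variables", and for continuous measures "Continuous variables will be compared with the Student t test and the Mann-Whitney test". None of the four tests uses age or the matching. That section does not say whether change or end-of-treatment values are compared.

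**The concern.** The design treats age as something to control, and the analysis then leaves it out. A statistical analysis plan may exist, but the protocol itself names the tests, so the choice is not simply left open.

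The consequences differ by aim. In Aim 1, matching forces the two groups to have similar ages, so age contributes little to the true sampling variance of the group difference. The unpaired standard error still counts age as random variation and is therefore too large. This holds for individual and for frequency matching, whenever age matters for the outcome. In Aim 2, randomisation protects the test, but any variance due to age stays in the error term. The stake is sensitivity: a real difference in a taxon is more easily missed in a small pilot.

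**Working it through.** **What the plan gives.** There is no microflora sample size or power to reproduce. The only sample-size figure, 35 per group, belongs to the inflammation endpoint. It follows from the log-odds formula with two occasions: (1.960 + 0.842)² × [1/(0.90 × 0.10) + 1/(0.63 × 0.37)] / (ln 0.189)² = 43.6, times (1 + 0.6)/2 = 0.8, gives 34.9. It is unaffected by this point.

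**Inputs.**
- From the FISH section: 22 stable CF children and 20 controls.
- Assumed: 11 per arm, if the 22 are split equally; 20 individually matched pairs for Aim 1; two-sided alpha 0.05.
- Assumed: R², the share of between-child variance explained by age, of 0, 0.10 or 0.30. The documents give no value.

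**Aim 1.** With perfect matching on age, the true variance of the difference is 2σ²(1 − R²)/n, while the unpaired test uses 2σ²/n. The true alpha is then about 2 × [1 − Φ(1.96/√(1 − R²))].
- R² = 0.10: 1.96/0.949 = 2.07, alpha about 0.039.
- R² = 0.30: 1.96/0.837 = 2.34, alpha about 0.019.

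A simulation of 20,000 runs agrees. The effect was set at 2.80 × √(2/20) = 0.89 SD, the size that gives 80% power by the normal approximation when matching is ignored.

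| R² | True alpha, unpaired | Power, unpaired | Power, paired |
| --- | --- | --- | --- |
| 0 | 0.051 | 77.2% | 75.1% |
| 0.10 | 0.039 | 79.0% | 79.7% |
| 0.30 | 0.020 | 81.7% | 88.9% |

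At R² = 0 the paired test loses about 2 points because it has 19 degrees of freedom instead of 38. A linear age term would leave 40 − 3 = 37.

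**Aim 2, end values, no baseline value in the model.** The t test is compared with a linear model that adds age, again at the effect that gives 80% by the normal approximation.

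| Per arm | R² | Power, t test | Power, age-adjusted |
| --- | --- | --- | --- |
| 11 | 0 | 75.5% | 72.9% |
| 11 | 0.10 | 75.6% | 77.4% |
| 11 | 0.30 | 76.1% | 87.3% |
| 35 | 0 | 79.2% | 78.5% |
| 35 | 0.10 | 78.7% | 82.0% |
| 35 | 0.30 | 79.2% | 90.4% |

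The type I error of the unadjusted t test was 0.050 to 0.053 throughout. The rows for 35 per arm are illustrative only, since that number was not derived for the microflora.

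**If change is analysed.** A child's age hardly moves in one month, so a stable additive age effect cancels from each child's change. The Aim 2 gains above are therefore upper figures. Aim 1 is cross-sectional, so this does not apply there.

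**The case against.** A reader might infer that chance age imbalance biases the randomised comparison. If ages are uniform on 2 to 18, the SD is 16/√12 = 4.6 years, and arm means differ by more than 2 years in 31% of trials with 11 per arm and 7% with 35. These are not error rates. Randomisation leaves the unadjusted test unbiased, and its standard error already includes such imbalance, as the simulated type I error confirms. It is the same loss of precision, not a second harm. Nor does it carry over to Aim 1, where matching limits imbalance.

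A reader might also take the gain to be established and large, for instance as equivalent to many more than 35 children per arm. The documents do not support this. The statement on age is general, names three other influences beside it, and gives no size within the range of 2 to 18 years. The 35 per arm and the 80% power belong to the inflammation endpoint.

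Four further points stand. A pre-treatment value of the same taxon would absorb much of a stable age effect, so age alone is not the best Aim 2 adjustment. With 22 CF children and 20 controls, complete one-to-one pairing is impossible, and no pairing scheme is described. FISH counts in a small field can be zero, which a plain log transform cannot handle. A conservative test also leaves any positive Aim 1 finding safe.

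What survives is the mismatch: a factor used for matching and already recorded appears in none of the named tests, for a primary endpoint.

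**Conclusion.** The point holds as a modest weakness of efficiency. In Aim 1 the stated tests are conservative to the extent that age explains the outcome. With 20 assumed pairs, alpha falls to about 0.04 (R² 0.10) or 0.02 (R² 0.30), and the power forgone is 0.7 points (79.7 − 79.0) or 7.2 points (88.9 − 81.7). In Aim 2 the stated test is valid. The precision lost on end values ranges from nothing at R² near 0 to about 11 points of power at R² 0.30 with 11 or 35 per arm, and it is small if change from baseline is analysed.

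All sizes rest on an assumed R² and on assumed group structures. The direction in Aim 1 needs only that age matters and that the groups were matched on it, and the protocol states both.

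**What to change.** In the microflora part of the statistical section:

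- **Aim 1:** analyse each taxon with a linear model containing group and age. If controls were individually matched, a paired analysis is an alternative; state which kind of matching was used.
- **Aim 2:** model the 1-month value on arm, the pre-treatment value of the same taxon, and age. The Study design text provides for a pre-treatment measurement, but Table 1 marks microflora only at Visit 2, so the two must be reconciled.
- **Both:** report adjusted differences with 95% confidence intervals, use a transform that handles zero counts, such as log(count + 1), and keep Mann-Whitney as a sensitivity analysis.

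The cost is a few sentences and one degree of freedom in Aim 1 or two in Aim 2. If age explains nothing, the age term costs about 3 power points at 11 per arm (75.5% to 72.9%) and under 1 point at 35 per arm. Demographic data are already collected at Visit 1 for the trial patients.
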